### 2.8. Statistical Analysis

Categorical variables will be presented using counts and frequencies, while continuous variables will be presented using mean, standard deviation, median, and interquartile range. Statistical significance will be declared when *p* < 0.05, without adjustment for multiple testing. Any comparisons between groups will be made using non-parametric tests, given the small sample size: Fisher’s tests for qualitative variables and Wilcoxon’s tests for quantitative data. Analyses will be performed using R (version ≥4.2). The normality of continuous variables will be assessed graphically. No replacements of missing data will be performed.

The main objective of the study will be achieved if the safety and performance sub-criteria are met for at least 12 out of the 15 volunteers. All secondary objectives will be analysed using descriptive tools except multi-omics analyses. 

A security interim analysis will be performed after the inclusion of the 3rd volunteer. This will focus strictly on the safety component of the primary outcome. No adjustments for alpha risk inflation are planned.

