### 1.3. Aims and Objectives

The primary objective of this clinical study is to demonstrate the safety and performance of the medical device. This objective is, thus, composite and will be achieved if both the safety and the performance of the MD are observed for at least 12 out of 15 volunteers. 

Each volunteer will ingest only one pill (the MD) containing tree modules.

The secondary objectives of this study are as follows: (1) to verify the safety of use of the MD for the collection of intestinal content, (2) to verify that the MD is transiting in the human intestinal tract, (3) to evaluate the capture of intestinal liquid by the MD, (4) to verify that the MD opened in the intestine, (5) to verify the state of the MD after collection, (6) to evaluate the sample’s functional potential and identify biomarkers (microorganisms, metabolites) via metagenomics and metabolomics, (7) to estimate the volunteer’s experiences about the MD ingestion and its use, and (8) to obtain the sample’s functional potential and identify biomarkers via culturomics for two subjects.

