### 2.6. Multi-Omics Analysis

Three meta-omics analysis will be performed during this clinical study (Figure 2). All samples will be analysed simultaneously and at the end of the study to avoid batch-related analysis biases, expect for culturomics. 

Metagenomics will be performed on one (small intestinal content (bacterial pellet obtained by centrifugation) + corresponding faeces) sample for each of the 15 healthy volunteers using 16S rRNA gene sequencing to determine the microbial composition of each sample. DNA from each sample will be extracted using Qiagen powerfecal pro Kits. Each sample will be amplified through PCR using a specific combination of primers specially designed and adapted for massive sequencing that allows us to capture the hypervariable region V3-V4 of the bacterial 16s rRNA [43]. To be able to construct the bacterial profile, each PCR product will be individually labelled. Each labelled product will pass through a primer-dimer removal protocol in order to allow us to increase the sequencing throughput. Once the PCR products are cleaned, they will be equimolarly pooled. The absolute abundance of 16S rDNA copy numbers representing bacterial biomass for each sample will be determined using qPCR.

Metabolomics will be performed on one (small intestinal content (liquid phase obtained by centrifugation) + corresponding faeces) sample for each of the 15 healthy volunteers. Small intestinal content samples collected by the MD and faecal matter will be analysed using liquid chromatography (Vanquish Flex, Thermo Fisher Scientific, Waltham, MA, USA) coupled with tandem Q Exactive Plus Orbitrap mass spectrometer (Thermo Fisher Scientific, Waltham, MA, USA) (LC-MS/MS). Untargeted and semi-targeted metabolomics will be performed in both positive and negative ionisation modes to characterise the metabolome of each sample. The main goal is to verify whether the volume collected by one module is sufficient to measure its metabolic fingerprint and to look for any differences with faecal matter. Principal component analysis on the metabolic fingerprints will allow us to conclude on this matrix difference. The semi-targeted approach will allow us to compare the relative amounts of approximately 45 preselected metabolites of interest between the small intestinal content and faeces.

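### The comparison of about 45 preselected metabolites, which serves the biomarker aim, is to be judged at unadjusted p<0.05 with no control of false discoveries

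*Protocol article*

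**What the plan says.** The general rule in Section 2.8 of the protocol article is "Statistical significance will be declared when *p* < 0.05, without adjustment for multiple testing". For comparisons between groups, that section names "Fisher’s tests for qualitative variables and Wilcoxon’s tests for quantitative data", without saying whether the Wilcoxon test is paired. It then states: "All secondary objectives will be analysed using descriptive tools except multi-omics analyses".

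Section 2.6 gives the one multi-item comparison that the article spells out. The semi-targeted metabolomics is to "compare the relative amounts of approximately 45 preselected metabolites of interest between the small intestinal content and faeces". For the untargeted fingerprints the same section names a different tool: "Principal component analysis on the metabolic fingerprints will allow us to conclude on this matrix difference". 16S sequencing is used to describe the bacterial composition of each sample, and no taxon-by-taxon test is described.

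Secondary objective 6 in Section 1.3 includes the aim to "identify biomarkers (microorganisms, metabolites) via metagenomics and metabolomics". Section 2.7 sets the sample size at 15 on grounds of feasibility.

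**The concern.** Refusing adjustment is a decision that the article states, so it is not a detail left to an analysis plan. The decision also lands where multiplicity is greatest. The study has one arm, the primary objective is a count of volunteers with no p-value, and the other secondary objectives are descriptive. What remains for p<0.05 is chiefly the omics comparison, and its metabolite panel alone has about 45 items.

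Identifying biomarkers means picking individual features. Under an unadjusted rule the share of false picks is not limited by anything in the plan and depends on how many metabolites truly differ, which is unknown. The article neither labels these tests exploratory nor describes a hierarchy or a validation step. At stake is the credibility of the metabolite findings under secondary objective 6.

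**Working it through.** **Inputs from the protocol article.** Per-test level 0.05, unadjusted (Section 2.8); m of about 45 metabolites (Section 2.6); 15 volunteers, each giving one intestinal sample and the corresponding faeces, hence 15 pairs (Sections 2.6 and 2.7).

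**Assumptions, because the article gives no figure.** Two-sided tests; the share of metabolites that truly differ (0 to 80%); power for those that differ (0.5 to 0.9); correlation between metabolites (0 to 0.8).

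**The plan's own figure.** The article derives no error rate or power that could be reproduced; 0.05 is an input. The exact two-sided signed-rank test with 15 pairs has an attainable size of 0.0479, consistent with that level.

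**Step 1: the panel with all 45 null and independent.**
- Expected false positives: 45 × 0.05 = 2.25.
- Chance of at least one: 1 − 0.95^45 = 0.901. At the exact size it is 1 − (1 − 0.0479)^45 = 0.890.

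**Step 2: part of the panel truly differs.** With m0 true nulls, expected false positives are FP = 0.05 × m0, and the chance of at least one is 1 − 0.95^m0. Expected true positives are TP = power × (45 − m0). The false share is approximated by FP/(FP + TP), a ratio of expected counts.

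| Truly differ | m0 | FP | Chance of at least one | False share, power 0.9 to 0.5 |
|---|---|---|---|---|
| 0% | 45 | 2.25 | 0.90 | every hit is false |
| 20% | 36 | 1.8 | 0.84 | 18% to 29% |
| 50% | 22.5 | 1.1 | 0.68 | 5% to 9% |
| 80% | 9 | 0.45 | 0.37 | 1% to 2% |

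For the 20% row: 1.8/(1.8 + 8.1) = 0.18 at power 0.9, and 1.8/(1.8 + 4.5) = 0.29 at power 0.5.

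**Step 3: correlation.** With all 45 null and equal correlation of 0.3, 0.5 or 0.8 (simulation of normal test statistics), the chance of at least one false positive is 0.78, 0.60 or 0.29. The expected number stays at 2.25, because expected counts add whatever the correlation; the false positives cluster in fewer trials.

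**Step 4: can adjustment work with so few volunteers?** The smallest two-sided signed-rank p is 2/2^15 = 0.000061 with 15 pairs and 2/2^12 = 0.00049 with 12 pairs. The strictest Benjamini-Hochberg step for 45 tests is 0.05/45 = 0.0011. Both values lie below it, so adjusted significance is attainable if the analysis is paired.

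**The case against.** The best defence is that this is a feasibility-sized pilot that openly declares unadjusted p-values. Section 3 expects real differences between faeces and small intestinal liquid, so a panel in which every null is true is not the plan's own expectation. If half or more of the metabolites differ, the false share is about 5–9% or lower, near or below the 5% that an adjustment would aim for. This stands as a limit on size. It does not remove the problem, because the true share is unknown and the plan has no safeguard if it is low.

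A second defence is that Section 2.8 takes multi-omics out of the descriptive set without naming its tests, and that an analysis plan not shown may hold omics methods. Applying the general rule to the panel is indeed a reading of the text, but a natural one. A plan that adjusted would depart from what the article states.

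A reader might also infer that thousands of untargeted features and all taxa will be screened at p<0.05. The article does not say so. It plans that "Untargeted and semi-targeted metabolomics will be performed in both positive and negative ionisation modes", but names principal component analysis for the fingerprints, which yields no p-value per feature, and it describes no taxon-level test. The problem would grow if such tests were run: 100 independent true nulls, an assumed number, give 5 expected false positives and a chance of at least one of 0.994.

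**Conclusion.** The point holds for the metabolite panel: about 45 comparisons under a biomarker aim, judged at p<0.05 "without adjustment for multiple testing". The chance of at least one false positive is up to about 90% with 45 independent true nulls. It falls to about 68% if half truly differ, to 37% if 80% do, and also falls with correlation. The more useful measure is the false share among the hits, which runs from 1–2% (80% differ) to 18–29% (20% differ), for assumed power between 0.9 and 0.5.

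Two stronger conclusions are tempting and not supported. One is that false discoveries are almost certain; this needs many, roughly independent true nulls, which Section 3 does not expect. The other is that the resulting list could not be told apart from noise; if half or more of the panel differs, most hits would be real.

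The effect is confined to the omics findings under secondary objective 6. The primary criterion of 12 out of 15 volunteers uses none of these tests.

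**What to change.** In Section 2.8, declare significance for the metabolite panel at a Benjamini-Hochberg false discovery rate of 5%, based on paired signed-rank tests of intestinal content against faeces within volunteer. Apply the same rule, separately within each omics family, to any taxon-level or feature-level tests that are run. Report q-values with effect sizes, and call hits candidate features. Unadjusted p<0.05 may stay for non-omics summaries.

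The change costs one sentence in the plan and one adjustment call in R, the software already named. The price is a shorter hit list; no more volunteers or samples are needed.

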## Abstract

The connection between imbalances in the human gut microbiota, known as dysbiosis, and various diseases has been well established. Current techniques for sampling the small intestine are both invasive for patients and costly for healthcare facilities. Most studies on human gut microbiome are conducted using faecal samples, which do not accurately represent the microbiome in the upper intestinal tract. A pilot clinical investigation, registered as NCT05477069 and sponsored by the Grenoble Alpes University Hospital, is currently underway to evaluate a novel ingestible medical device (MD) designed for collecting small intestinal liquids by Pelican Health. This study is interventional and monocentric, involving 15 healthy volunteers. The primary objective of the study is to establish the safety and the performance of the MD when used on healthy volunteers. Secondary objectives include assessing the device’s performance and demonstrating the difference between the retrieved sample from the MD and the corresponding faecal sample. Multi-omics analysis will be performed, including metagenomics, metabolomics, and culturomics. We anticipate that the MD will prove to be safe without any reported adverse effects, and we collected samples suitable for the proposed omics analyses in order to demonstrate the functionality of the MD and the clinical potential of the intestinal content.

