## 2. Experimental Design

This investigation is an interventional and monocentric study conducted at the Grenoble Alpes University Hospital on 15 healthy volunteers. 

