The sample preparation consists first in screening for the module in the collected faecal matter. If no module is detected, the faeces collection continues. If at least one, or all modules, are detected in the collected faecal sample, the modules are recovered. The collected modules are then washed and assessed (e.g., observed leakage), weighted (to estimate the intestinal liquid volume sampled), and the content is recovered by centrifugation, leading to a sample that is divided into a pellet (bacterial content) and supernatant (intestinal metabolites). The supernatant is transferred into a new Eppendorf tube for metabolomic analysis, and its pH is measured using a pH paper indicator. The pellet is used for metagenomic analysis. For each volunteer, one module is used for multi-omics analysis, and the remaining ones (if any) are stored in the biological collection in case of a complementary analysis and as backup. If a module is contaminated by faecal matter due to leakage, the back-up module is used for the multi-omics analysis. Faecal samples are also collected from healthy volunteers and will be analysed by the same approaches as the intestinal content collected with the medical device. All samples are stored at −80 °C until analysis. 

For two volunteers, culturomics analysis will be performed if at least two out of the three modules per healthy volunteer are recovered and contain more than 50 µL, displaying no faecal contamination. The first retrieved module will be used for metagenomics and metabolomics analysis, and the second retrieved module will be used for culturomics analysis and will be directly placed in an anaerobic bag to preserve strictly anaerobic bacteria. The samples will be rapidly sent to the culturomics platform at +4 °C. In case the third module is contamination-free, it will serve as a back-up for analysis. 

The design of the study is illustrated in Figure 1.

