### 2.7. Sample Size

The number of subjects to be included is set at 15 healthy volunteers to meet practical feasibility requirements. Any patient whose data are deemed unusable, notably due to sample transport lasting >4 h, will be replaced to obtain 15 usable samples, up to a limit of 20 patients in total.

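### The planned tests are worded for independent groups, but the only comparison described, module content against faeces, is paired within volunteer

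*Protocol article*

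**What the plan says.** Section 2 describes one group and no comparator arm: "This investigation is an interventional and monocentric study conducted at the Grenoble Alpes University Hospital on 15 healthy volunteers". Section 2.7 sets that number on feasibility grounds: "The number of subjects to be included is set at 15 healthy volunteers to meet practical feasibility requirements".

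The contrast of interest lies within the volunteer. The Abstract lists among the secondary aims "demonstrating the difference between the retrieved sample from the MD and the corresponding faecal sample". Section 2.5 states: "Faecal samples are also collected from healthy volunteers and will be analysed by the same approaches as the intestinal content". Section 2.6 plans sequencing on one small intestinal sample together with the "corresponding faeces) sample for each of the 15 healthy volunteers using 16S rRNA gene sequencing", uses the same one-plus-one arrangement for metabolomics, and intends to "compare the relative amounts of approximately 45 preselected metabolites of interest between the small intestinal content and faeces". For the untargeted fingerprints it names another tool: "Principal component analysis on the metabolic fingerprints will allow us to conclude on this matrix difference".

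Section 2.8 then gives the tests: "Any comparisons between groups will be made using non-parametric tests, given the small sample size: Fisher’s tests for qualitative variables". The sentence goes on to Wilcoxon's tests for quantitative data, with significance at p < 0.05. The same section makes every secondary objective descriptive apart from multi-omics. It does not mention pairing.

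**The concern.** The testing sentence assumes independent groups, and the article describes none. Wherever a hypothesis test is applied to the multi-omics data, the two values compared come from the same person.

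Fisher's exact test sees only the two totals of positives. The evidence in paired binary data lies in the discordant pairs, which those totals do not reveal. The rank-sum test likewise treats 15 module values and 15 faecal values as 30 unrelated observations. If the two samples from one person are positively correlated, the rank-sum test is too conservative and loses power. If they are negatively correlated, it rejects too often.

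At stake is the reliability of the tests behind the module-versus-faeces difference, including the roughly 45 preselected metabolites.

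**Working it through.** There is no power figure in the article to reproduce, because the sample size rests on feasibility. The check is therefore whether the named tests suit the design, and how much it matters if they do not.

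**Inputs from the article:** 15 volunteers, one module sample and one faecal sample each, giving up to 15 pairs; significance at 0.05.

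**Assumed:** two-sided testing, normal data with equal variances, a true shift of 0 or 0.8 SD, and within-volunteer correlation ρ from −0.3 to 0.7. The article gives neither a shift nor a correlation.

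**1. Quantitative variables.** The mean module-minus-faeces difference has variance 2σ²(1 − ρ)/n. An unpaired test in effect uses 2σ²/n. That is too large when ρ > 0 and too small when ρ < 0. A paired test works with the standardised shift 0.8/√(2(1 − ρ)):

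- ρ = 0: 0.8/√2.0 = 0.57
- ρ = 0.3: 0.8/√1.4 = 0.68
- ρ = 0.5: 0.8/√1.0 = 0.80
- ρ = 0.7: 0.8/√0.6 = 1.03

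Simulation of 15 pairs, 4,000 runs per setting:

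| ρ | Rank-sum power | Signed-rank power | Rank-sum type I error |
|---|---|---|---|
| 0 | 52% | 51% | 4.3% |
| 0.3 | 54% | 67% | 2.2% |
| 0.5 | 53% | 80% | 0.8% |
| 0.7 | 56% | 95% | 0.2% |

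At ρ = −0.3 the rank-sum type I error rises to between 7% and 8%. The signed-rank type I error stays between about 4% and 5% throughout. The Monte Carlo standard error near 50% power is √(0.5 × 0.5/4000) = 0.8 percentage points. Repeat runs, one set with 20,000 replicates, gave the same picture to within a point or two.

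**2. Binary variables.** With b and c the two kinds of discordant pair, exact McNemar is p = 2 × P(X ≤ min(b, c)), where X is binomial (b + c, ½). Three illustrative tables of 15 pairs:

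- 10/15 against 4/15, discordant 6:0. McNemar: 2 × 1/64 = 0.031. Fisher: 0.066.
- 10/15 against 4/15, discordant 8:2. McNemar: 2 × (1 + 10 + 45)/1024 = 0.109. Fisher: again 0.066.
- 14/15 against 8/15, discordant 7:1. McNemar: 2 × (1 + 8)/256 = 0.070. Fisher: 0.035.

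The first two tables have the same totals, so Fisher cannot tell them apart, while the paired p-values lie on opposite sides of 0.05. In the third, Fisher is significant and McNemar is not.

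The direction of error follows the association between the two samples. In the first table 4 volunteers are positive on both samples, against 10 × 4/15 = 2.67 expected under independence, and Fisher is the less sensitive test. In the third, 7 are positive on both against 14 × 8/15 = 7.47 expected, a slightly negative association, and Fisher is the more liberal one.

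**The case against.** A reader might infer that the plan commits to unpaired tests throughout and that its p-values will therefore be wrong. The article does not support that.

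- **The Wilcoxon variant is open.** The name covers both the signed-rank and the rank-sum test. Section 2.6 speaks of corresponding faeces, so the authors knew that the samples were linked. The between-groups wording next to Fisher points towards rank-sum but does not settle it, and the choice could properly be left to an analysis plan. This stands.
- **Fisher has no stated application here.** The module-faeces comparisons described are mainly quantitative or multivariate: 16S composition, bacterial load by qPCR, relative metabolite amounts, fingerprints by principal component analysis, diversity. No presence/absence test is specified. This limits the harm, but Fisher is still the test named for qualitative variables, and no independent groups are described to which it could apply.
- **The loss depends on an unknown correlation.** At ρ = 0 there is none, and at 0.3 it is modest. The Introduction argues that faeces do not represent the intestinal microbiome, so a low correlation is plausible. This stands, and it is why the whole range is shown.
- **The consequences are limited.** The primary objective is a count rule, the other secondary objectives are descriptive, and this is a pilot. With positive correlation the rank-sum error is lost power rather than false claims. This also stands and bears on severity.

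An unseen analysis plan does not dispose of the point. Section 2.8 names a test and a framing that do not match the design, which is more than leaving a detail out.

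**Conclusion.** The point holds in a limited form. The only comparison described is paired within volunteer, while the testing sentence is written for independent groups. Fisher's exact test is unsuitable for any qualitative module-faeces comparison. For quantitative variables the established fault is an unspecified test. If signed-rank is meant, nothing is wrong beyond the wording. If rank-sum is meant, the power cost under the assumed 0.8 SD shift runs from nothing at ρ = 0 to about 40 percentage points at ρ = 0.7, and the type I error from between 7% and 8% at ρ = −0.3 down to about 0.2% at ρ = 0.7.

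These sizes rest on the assumed shift, correlations and normality. That module against faeces is the only comparison is inferred from the article, which describes no other. The rule of 12 out of 15 is unaffected either way. Severity is moderate and confined to the secondary multi-omics objective.

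**What to change.** Amend the testing sentence in section 2.8 to say that:

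- module-versus-faeces comparisons are paired within volunteer and restricted to volunteers with both samples, with the number of pairs reported;
- quantitative variables are compared with the Wilcoxon signed-rank test, with a stated handling of zero differences and ties, which are likely in taxa data;
- any binary comparison uses the exact McNemar test in place of Fisher.

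This needs no new data or participants. Section 2.6 places the omics analyses at the end of the study, culturomics excepted, and the Data Availability statement reports no data yet, so on the article's account the change can be made before results are known.

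There is a small cost. Exact McNemar needs at least six discordant pairs, all in one direction, to reach p < 0.05: five give 2 × 1/32 = 0.0625 and six give 2 × 1/64 = 0.031. With at most 15 pairs, some binary comparisons will be unable to reach significance.
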